#### 4- Method of investigation retained

The study is observational, prospective, open, monocentric carried out under the conditions of daily practice, part of the multidisciplinary consultation for chronic stubborn pain at the Lannion-Trestel Hospital Center.

5

##### 4-1. During the initial visit, the investigating doctor :

- gives the patient the information note, answers their questions and obtains their oral consent,
- verifies that the inclusion and exclusion criteria are respected,
- completes, in the data collection notebook assigned to the patient, according to the methodology developed in § 3-1,
- fills in the section "treatments for temporomandibular osteoarthritis", all treatments being authorized according to the rules of an observational study, provided they are collected,
- checks that the dental panoramic X-ray is less than 12 months old and asks for another one if necessary, as recommended before any intra-articular injection into the ATM.
- schedules or performs the intra-articular injection of HAppymini® hyaluronic acid himself. The injection may be performed the same day or for organizational reasons within a maximum period of 15 days, in order to limit the risk of variation in the clinical condition between the assessment and the date of the injection.

##### 4-2. During the intermediate visit on D90 (+ or - 14 days) and the final visit on D180 the investigator:

- postpones to the end of the CRF any changes in concomitant treatments for TMJ osteoarthritis,

[figure not shown]

- reports any adverse events that have occurred since the day of the injection, and will specify whether or not they are attributable to the treatment or the procedure,
- completes the CRF according to the methodology developed in § 3-2.

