**3-2. During the visits at 3 (D90) and 6 months after the injection (D180) the following elements will be collected:**

- TMJ pain when chewing (Likert 0-10),
- TMJ pain on palpation (Likert 0-10),
- IID at maximum mouth opening (mm)
- Patient satisfaction with the treatment (4-point Likert where 0 means "Not satisfied" and 3 means "Very satisfied")
- The patient's perception of the effectiveness of the treatment (4-point Likert where 0 means "Not effective" and 3 means "Very effective")
- The patient's perception of the reduction in pain in 6 categories: [0%]; [1-24%], [25-49%], [50-74%], [75%-99%], [100%]
- The change in his consumption of analgesics or anti-inflammatories compared to D0 ([YES/NO] and if [YES] quantification on a 5-point Likert scale ([1-24%], [25-49%], [50-74%], [75%-99%], [100%]))
- Any adverse effects during the D90 visit (to ensure quality monitoring of the treatment)

[figure not shown]

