### 5-1. The treatment

It will consist of 1 single intra-articular injection into the painful temporomandibular joint of 1ml of a viscosupplement marketed for this indication (HAppymini®, Laboratoire de Rhumatologie Appliquée, Labrha, Lyon). HAppymini® is a sterile, pyrogen-free and isotonic viscoelastic solution of cross-linked sodium hyaluronate in a buffered physiological solution. The sodium hyaluronate contained in this injectable medical device for intra-articular use is obtained by bacterial fermentation and is present at a concentration of 1.6%. It also contains mannitol at a concentration of 3.5% and comes in the form of a 1 ml glass syringe containing 1 ml of solution. The syringe is presented in an individual sterilized protective case. Packaging available: box of 1 syringe, bearing the indications for use and a leaflet, which must be stored between +2°C and +25°C for 30 months (MD technical sheet and CE marking in appendix 4).

The injector may be the investigator himself, or another doctor he has designated.

**5-2. The injection technique** will be that described in the book "Gestures in rheumatology" (4) and carried out according to the usual recommendations for any intra-articular injection, according to a perfectly aseptic administration technique (cutaneous asepsis, wearing of surgical gloves).

**5-3. After the injection**, patients can go home, observing the usual precautions that follow any intra-articular injection. The investigator is

[figure not shown]

free of the type of joint saving it will provide (absence, relative, wearing a splint) and its duration, provided it is collected in the CRF.

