## **10-Vigilance and management of adverse events**

As this study is observational and falls within current practice, it is not mandatory to include a section for collecting adverse events.

Nevertheless, the scientific committee and the sponsor wanted a collection as careful as in the interventional studies to be carried out.

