#### **10-4. List of expected adverse events**

- Adverse events related to the injected viscosupplement: The most common (2 to 10%) is transient pain in the treated joint, lasting a few hours to a few days after the injection. More rarely, a painful effusion can be observed (<5%). However, these reactions generally disappear after a few days without any treatment. During its operation, no general reaction was observed with the DM used.
- Adverse events related to the practice of injection: During or after intra-articular injection, transient pain or hematoma at the puncture site may appear. The risk of joint infection is estimated between 1/20,000 and 1/50,000 injections.

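### Nothing scheduled covers the days after injection: the first planned adverse-event collection is at D90, so short-lived non-serious reactions will probably be under-counted

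*Protocol*

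**What the plan says.** **After the injection.** Section 5-3 says that "patients can go home, observing the usual precautions that follow any intra-articular injection". The document describes no telephone call, visit or patient diary between that moment and D90.

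**Scheduled collection.** Section 4-2 sets the timing ("During the intermediate visit on D90 (+ or - 14 days) and the final visit on D180 the investigator") and the task: the investigator "reports any adverse events that have occurred since the day of the injection". Section 3-2 counts both visits from the injection ("During the visits at 3 (D90) and 6 months after the injection (D180) the following elements will be collected"). Its own list names adverse effects at one visit only: "Any adverse effects during the D90 visit (to ensure quality monitoring of the treatment".

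**Expected reactions.** Section 10-4 gives the most common product reaction, at 2 to 10%, as "transient pain in the treated joint, lasting a few hours to a few days after the injection". It adds painful effusion at under 5% and says that these product reactions generally resolve in a few days untreated. Pain or hematoma at the puncture site is listed separately as a procedure reaction, with no duration.

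**The standard set.** Section 10 notes that collecting adverse events is not mandatory in this observational study, then says that "the scientific committee and the sponsor wanted a collection as careful as in the interventional studies to be carried out".

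**Duties on the investigator.** Section 10-1 requires every adverse event, non-serious ones included, to be noted on the form, without tying this to visits. Sections 10-1 to 10-3 add 24-hour serious-event reporting, causality assessment and follow-up to recovery or stabilization.

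**The concern.** The reactions the protocol expects most often begin and end in a period when nobody is scheduled to ask about them. A mild reaction that settles untreated gives the patient little reason to telephone. The expected reaction is also joint pain, in patients enrolled because of joint pain, so a brief flare is hard to separate from background pain when it is asked about three months later.

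At stake is the early-reaction rate. In a cohort with one injection per patient, that is the main safety figure the data can offer. Under-ascertainment pushes it downward, and in a group of this size a low or zero count could then come from the collection method as easily as from good tolerance. Because Section 10 states a high standard of collection, a reader would have no warning of this.

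**Working it through.** **1. Inputs.**
- 44 patients to be included for 40 complete files, 10% loss (Section 7). Check: 40 × 1.10 = 44, as stated; 40 / 0.90 = 44.4. The point does not depend on this difference.
- D90 ± 14 days (Section 4-2), counted from injection (Section 3-2).
- Transient joint pain 2 to 10%, lasting hours to days (Section 10-4).
- Capture rate, meaning the share of true reactions that get recorded: not given in the document. Values from 100% down to 20% are assumptions.

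**2. Time to first scheduled collection.** 90 − 14 = 76 and 90 + 14 = 104, so day 76 to 104 after injection. Section 4-1 allows a delay between assessment and injection ("The injection may be performed the same day or for organizational reasons within a maximum period of 15 days"). If D90 were counted from the D0 visit instead, the earliest contact would be 76 − 15 = day 61. The conclusion is the same.

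**3. Gap after the reaction has ended.** Taking a few days as 3 to 7 (assumption): 76 − 7 = 69 days at the shortest, 104 − 3 = 101 days at the longest.

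**4. Expected cases of transient pain.** n × p: 44 × 0.02 = 0.88 and 44 × 0.10 = 4.4.

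**5. Chance of recording no case.** With true rate p and capture s, P(none) = (1 − p·s)^44. At p = 5%:

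| Capture s (assumed) | Expected recorded, 44·p·s | P(none recorded) |
|---|---|---|
| 100% | 2.2 | 0.95^44 = 0.105 |
| 80% | 1.76 | 0.96^44 = 0.166 |
| 50% | 1.1 | 0.975^44 = 0.328 |
| 20% | 0.44 | 0.99^44 = 0.643 |

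At the ends of the protocol's range, going from full to half capture moves P(none) from 0.411 to 0.643 at p = 2% and from 0.010 to 0.105 at p = 10%.

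**6. Patients who miss scheduled collection.** 44 × 0.10 = 4.4, so at most about 4 patients at the planned loss. This is an upper bound, because the 10% covers the whole study and some patients will leave after D90.

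**7. Sections 3-2 and 4-2 side by side.** Section 3-2 names adverse effects at D90 only. Section 4-2 has the investigator report them at both D90 and D180. Both cannot describe the same case report form.

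**The case against.** Several stronger readings are tempting, and the document does not support them.

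- *Reactions are collected only by recall, and a patient lost before D90 gives no safety data.* Section 10-1 requires all adverse events to be noted at any time, so a spontaneous report on day 2 can be recorded. Section 10-4 says pain or hematoma may appear during the injection, when a doctor is present. What is missing is a scheduled route by which the investigator would learn of a mild reaction at home.
- *The Section 10 standard is not met at all, or serious events will arrive months late.* The adverse-event form, 24-hour reporting, causality assessment, coding and follow-up are all specified. The 24-hour clock runs from learning of the event, but nothing in the document shows serious events going unnotified until D90. The shortfall is confined to short-lived non-serious reactions.
- *Every expected reaction is over within days.* That statement covers the product reactions. No duration is given for hematoma.

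The other side can also say that the aim is to find predictors of response, that no safety endpoint is planned, that Section 10 does not define careful collection by frequency of contact, and that the patient information note, which is not shown, may ask patients to report reactions. These points limit the weight of the concern. They do not remove it: an instruction to call would still produce spontaneous reports, and the protocol chose its own standard. Finally, the capture rates are assumed, so the calculation shows sensitivity and does not estimate the loss.

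**Conclusion.** The point holds in a limited form. Between the patient's departure and day 76 to 104, no scheduled contact or patient record exists, while the commonest expected reaction lasts hours to days. Its recording therefore depends on spontaneous report or about three months' recall, and its rate will probably be under-counted. That does not match the standard in Section 10.

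The timing follows directly from the text. The size does not: 0.9 to 4.4 expected cases comes from the protocol's own range, but the rise in the chance of a zero count, from 10% to between 17% and 64% at a true 5% rate, rests on assumed capture of 80% to 20%. The analysis of response predictors and the serious-event procedures are unaffected. This is an inexpensive improvement to safety ascertainment and does not undermine the study. The mismatch between Sections 3-2 and 4-2 needs correcting in any case.

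**What to change.** **Preferred.** In Sections 4-1, 4-2 and 10-1, add a one-page reaction card handed to each patient at injection and covering the first week: pain 0-10, swelling, bruising, duration and any medical contact. The patient brings it to D90 or returns it to the site. The prepaid envelopes in Section 6 should not be used, since they are supplied to investigators for answering data queries. Report the early-reaction rate from the card over all injected patients and state how many cards came back, so that a missing card is not silently read as no reaction. Use recall at D90 and D180 as a second source.

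**If declined.** Narrow the Section 10 statement to what the schedule supports, and report the early-reaction rate as a likely lower bound.

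**In either case.** Make Sections 3-2 and 4-2 agree on whether adverse events are collected at D90 only or at D90 and D180.

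**Cost.** No extra visit or procedure. The card is a small form beyond the routine questionnaires that Section 1 says are the only constraint on the patient, so that sentence needs a matching edit, and the added data should be covered by the data-processing authorizations in Section 11-1. Some cards will not be returned, and the recorded reaction rate will probably be higher than recall alone would give. The fallback costs only wording.

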## 5- Treatment and injection technique

[figure not shown]

### 5-1. The treatment

It will consist of 1 single intra-articular injection into the painful temporomandibular joint of 1ml of a viscosupplement marketed for this indication (HAppymini®, Laboratoire de Rhumatologie Appliquée, Labrha, Lyon). HAppymini® is a sterile, pyrogen-free and isotonic viscoelastic solution of cross-linked sodium hyaluronate in a buffered physiological solution. The sodium hyaluronate contained in this injectable medical device for intra-articular use is obtained by bacterial fermentation and is present at a concentration of 1.6%. It also contains mannitol at a concentration of 3.5% and comes in the form of a 1 ml glass syringe containing 1 ml of solution. The syringe is presented in an individual sterilized protective case. Packaging available: box of 1 syringe, bearing the indications for use and a leaflet, which must be stored between +2°C and +25°C for 30 months (MD technical sheet and CE marking in appendix 4).

The injector may be the investigator himself, or another doctor he has designated.

**5-2. The injection technique** will be that described in the book "Gestures in rheumatology" (4) and carried out according to the usual recommendations for any intra-articular injection, according to a perfectly aseptic administration technique (cutaneous asepsis, wearing of surgical gloves).

**5-3. After the injection**, patients can go home, observing the usual precautions that follow any intra-articular injection. The investigator is

[figure not shown]

free of the type of joint saving it will provide (absence, relative, wearing a splint) and its duration, provided it is collected in the CRF.

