The objective of this research is therefore not to demonstrate the effectiveness of viscosupplementation in painful degenerative pathologies of TMJ **but to seek clinical factors predicting the success or failure of treatment** such as clinical severity before the injection, the presence of a limitation of the mouth opening or the duration of the symptoms.

For this we place ourselves **in the conditions of daily practice, in patients with symptomatic temporomandibular osteoarthritis with no other selection criteria** than the opinion of the investigator concerning the merits of viscosupplementation and the agreement of the patient participating in the research. **It in no way modifies the patient's therapeutic management and imposes no other constraint on him than filling in simple questionnaires commonly used in daily practice, in the monitoring of this pathology.**

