### **Exclusion criteria:**

- Patients with a contraindication to viscosupplementation with HAppymini® hypersensitivity to hyaluronic acid or mannitol) or to

[figure not shown]

intra-articular injection procedure (current general infectious disease, infected skin lesions near the injection site, dental infection).

- Patients in whom the evaluation of the effectiveness of the treatment could not be carried out reliably:
  - Patients who received a viscosupplement in the target joint during the previous 6 months,
  - Patients who have received an intra-articular injection of corticosteroids in the target joint during the previous 3 months,
  - Patients undergoing planned surgery within 3 months of injection that may interfere with follow-up or evaluation,
  - Patients who do not speak French or who are unable to give their consent personally.

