#### 3-1. During the selection visit (D0), the following elements will be collected:

- Demographics (gender, age, height, weight)
- Length of pain
- The target side

[figure not shown]

- Previous treatments for the pathology evaluated (NSAIDs, analgesics, muscle relaxants, infiltration of corticosteroids into the painful TMJ, injections of hyaluronic acid into the painful TMJ, specific rehabilitation of the oral sphere, wearing an occlusal splint)
- The search for bruxism, noises and / or crackles during chewing,
- TMJ pain on chewing measured on an 11-point numerical scale, "0" meaning "no pain" and "10" meaning "intolerable pain" (Likert 0-10),
- TMJ pain on palpation (Likert 0-10),
- The inter-incisor distance (IID) at the maximum opening of the mouth, measured in millimeters using a caliper.

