#### 8-2. The endpoint is the response to treatment.

The aim of the study being the search **for predictive factors of response to treatment**, it is not relevant to determine a primary endpoint. We will study the possible correlation between the response to the treatment and the level of pain on D0, the duration of the symptoms, the presence of a limitation of the mouth opening, and the existence of radiological lesions of osteoarthritis on the panoramic dental picture.

[figure not shown]

The response to the treatment will therefore be estimated by 3 complementary methods and for each of them the predictive factors of response (YES/NO) will be studied. Each patient will be classified into a treatment response category: YES or NO depending on:

1. The patient's assessment of the effectiveness (effective and very effective = YES, not or only slightly effective = NO),
2. Reduction in pain of at least 3 points or at least 50% on the Likert scale.
3. The degree of patient satisfaction (Very satisfied and fairly satisfied = YES, little or not satisfied = NO),

We will look for predictive factors of response or non-response, first in univariate analysis then in multivariate analysis by integrating all the factors with a  $P < 0.1$  in the univariate analysis, as well as possible confounding factors such as age, gender, taking NSAIDs, wearing a tray.

The main analysis will be carried out on the per-protocol population including only patients for whom all the data at D0 and D180 are available, then confirmed by ITT. For patients who do not have D180 data, the latest data available (D90) will be used (LOCF). The regression coefficients of the multivariate models (ANCOVA and mixed model) will be considered significant if the degrees of significance are less than 5%. Statistical analyzes will be performed with XLStat software.

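### One joint is injected, but pain in the opposite TMJ is not recorded and the pain scores name no side, so untreated disease on the other side can make a successful injection count as a non-response

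*Protocol*

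**What the plan says.** **Treatment.** Protocol 5-1 specifies "1 single intra-articular injection into the painful temporomandibular joint", so one joint per patient.

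**Entry.** Section 1 places the study "in patients with symptomatic temporomandibular osteoarthritis with no other selection criteria" beyond the investigator's opinion and the patient's agreement. Neither the inclusion nor the exclusion criteria restrict entry to one-sided disease. The exclusions meant to protect the evaluation look at one joint where they concern past injections, for example "Patients who received a viscosupplement in the target joint during the previous 6 months".

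**Data.** At D0, section 3-1 collects "The target side" and no item on the other joint. In 3-2 the follow-up item reads "TMJ pain when chewing (Likert 0-10" with no side, and the palpation item is equally silent. Satisfaction, perceived effectiveness and perceived pain reduction are asked of the patient as a whole.

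**Analysis.** Section 8-2 defines three YES/NO responses: perceived effectiveness, satisfaction, and "Reduction in pain of at least 3 points or at least 50% on the Likert scale". The last names neither the side nor which pain scale is meant. The named predictors are D0 pain, symptom duration, limited opening and radiological lesions. The adjustment list is "possible confounding factors such as age, gender, taking NSAIDs, wearing a tray". The state of the opposite joint appears in neither list.

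**The concern.** The study's only question is what separates success from failure after the injection. A second painful joint that is left untreated is a structural reason for a one-joint injection to look like a failure: the injected side improves, yet the patient still hurts when chewing and rates the result accordingly. The listed data cannot show this.

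Two consequences need to be kept apart. The first is misclassification: some patients whose target joint responded are scored NO, which weakens any true predictor. The second is confounding: if bilateral disease is commoner in severe or long-standing cases, its effect would be credited to D0 pain, duration or limited opening. The second needs that extra condition; the first does not.

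A statistical analysis plan cannot repair this later, because opposite-joint pain that was never recorded cannot be adjusted for.

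**Working it through.** The protocol states no figure on laterality, so there is none to reproduce. All inputs below are assumptions, except the response rule and the 40 complete files (sections 8-2 and 7).

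**1. Can the pain response flip?** Assume target pain of 6.5 at D0 and a fall of 3 on the injected side, to 3.5. The opposite joint stays unchanged, and the patient reports the worse joint.

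| Opposite joint | Reported D0 → D180 | Fall | Response |
|---|---|---|---|
| not painful | 6.5 → 3.5 | 3.0 | YES |
| 1 point less (5.5) | 6.5 → 5.5 | 1.0 (15%) | NO |
| 2 points less (4.5) | 6.5 → 4.5 | 2.0 (31%) | NO |
| 3 points less (3.5) | 6.5 → 3.5 | 3.0 | YES, just |
| 4 points less (2.5) | 6.5 → 3.5 | 3.0 | YES |

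If the score refers to the target side, every row is 6.5 → 3.5 and nothing flips.

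**2. The same with variation between patients.** Simulation of 400,000 patients: D0 pain SD 1.5, fall SD 2, measurement error SD 0.8, integer scores.

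- One-sided disease: about 61% YES.
- Worse joint reported, gap of 1, 2 or 3 points: about 14%, 30% or 47% YES. At a 2-point gap, about 51% of target-joint responders are scored NO.
- Worse joint reported, gap of 4 points: 55–59% YES, depending on how much the gap varies between patients.
- Report midway between the worse joint and the target joint, gap of 1, 2 or 3: about 39%, 50% or 58%.
- Average of both joints reported, gap of 1 to 3: about 30–36%. Here a 4-point gap is not harmless: (6.5 + 2.5)/2 = 4.5 falls to (3.5 + 2.5)/2 = 3.0, a drop of 1.5 points or 33%, which is a NO.

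**3. Misclassification without confounding.** Let R be the true target-joint response, b the share with a painful opposite joint, and m the chance that it flips a YES to a NO. Then observed YES = R(1 − bm). With R = 0.70 and the same b in both halves of a split by duration or severity:

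- b = 0.2, m = 0.25: 40 × 0.70 × 0.05 = 1.4 true responders scored NO.
- b = 0.3, m = 1: 40 × 0.70 × 0.30 = 8.4 scored NO.
- The odds ratio for the split stays at 1.00. A real predictor is diluted: multiplying both response rates by the same factor below 1 pulls their odds ratio towards 1.

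**4. Confounding, only if b differs between the halves** (20 v 20 patients, R = 0.70 in both, two-sided normal approximation):

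| b, low v high half | m | Observed YES | Odds ratio | Chance of P < 0.1 |
|---|---|---|---|---|
| 0.1 v 0.3 | 0.25 | 68.3% v 64.8% | 0.85 | about 11% |
| 0.1 v 0.5 | 0.5 | 66.5% v 52.5% | 0.56 | about 23% |
| 0.1 v 0.5 | 1 | 63% v 35% | 0.32 | about 55% |

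With no true effect the last column would be 10%.

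Linking this to step 2 at a 2-point gap, suppose 50% of long-duration and 20% of short-duration patients are bilateral. YES is 0.61 − 0.31 × 0.5 = 0.455 v 0.61 − 0.31 × 0.2 = 0.548. The odds ratio, short v long, is (0.548/0.452)/(0.455/0.545) = 1.45. The chance of passing the P < 0.1 screen rises from 10% to about 16%, and of reaching P < 0.05 from 5% to about 9%.

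**The case against.** The strongest reply is that the protocol speaks throughout of a target joint and a target side. The pain items follow that entry in the D0 list, and palpation is naturally done on one joint. On that reading the pain response is largely protected and the figures in steps 1 and 2 fall away. This stands as a plausible reading, but the text does not state it, and one added phrase would settle it.

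A second reply is that effectiveness and satisfaction are asked about the treatment, so a patient can judge the injected side alone. Some can. These are still whole-patient ratings, and the documents give no basis for assuming that pain on the other side leaves them untouched. No figure here measures how much it does.

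Third, there is partial cover. The adjustment list is open-ended, the panoramic film is required for everyone, changes in TMJ treatment are collected, and the CRF is not shown. Opposite-side lesions could thus perhaps be read from the film afterwards. Opposite-side pain is not among the listed data and could not.

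A reader might go further and infer that any effect of duration or severity found here would be an artefact, or that admitting bilateral patients was a mistake. The documents support neither. They give no frequency of bilateral pain and no link between it and duration or severity; the plural joints in the section 1 symptom description are generic. Broad entry is a deliberate choice for a daily-practice study that calls itself exploratory.

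**Conclusion.** The gap is real: one joint is treated, the condition of the other is not recorded, and the side of the pain scores is unstated. Untreated opposite-joint pain can turn a success into a NO, most directly for effectiveness and satisfaction, and for the pain response if its scores are not target-specific.

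The size cannot be fixed from the documents. For the pain response it runs from nil (target-specific scores) or small (worse joint reported, opposite joint 4 or more points less painful) to large (both joints similarly painful). A spurious predictor requires bilaterality to be related to that predictor. Without that relation the odds ratio for a null factor stays at 1.00, and the cost is misclassification and lost power. With it, the illustrations run from negligible (0.85) to marked (0.32), and the worked duration example (1.45) is modest. This is a cheap improvement, not a defect that invalidates the study.

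**What to change.** - **Section 3-1:** add one D0 item on the opposite TMJ: pain 0–10, and osteoarthritic lesions yes/no on the panoramic film already required.
- **Sections 3-1 and 3-2:** state that the chewing and palpation scores refer to the target side.
- **Section 8-2:** name a painful opposite joint at D0 as a candidate factor or confounder for all three responses, and repeat the main analysis in patients with one-sided pain.

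The cost is one CRF line from an examination and a film already done, one more model term in about 40 patients, and a smaller subset for the sensitivity analysis. Treatment and eligibility are unchanged.
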